#### Concealment mechanism

The allocation sequence will be uploaded upon study start. As soon as the eCRF is unlocked for real study data entry, there will be access for the study team to see the sequence.

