#### Participant timeline

The study period consists of screening and enrolment, allocation, observation time and closeout. Screening and enrolment will be performed within 48 h after ICU admission. Allocation is defined as the day of start of enteral feeding. Closeout is defined as the end of the seventh day of observation (or day of discharge from the ICU, if earlier than 7 days).

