##### Day of inclusion (t_−1_)

We plan to perform the ultrasound and muscle biopsy on the day of study inclusion of eligible patients. Depending on time of ICU admittance, staff resources and opening hours of the Biobank storage, we will not always be able to do so. Therefore, if both the ultrasound and biopsy can be performed before 3:00 pm on the day of inclusion, enteral feeding will be initiated the next morning at 6:00 am. Otherwise, the procedures will be postponed to the next day and start of enteral feeding will be the following morning at 6:00 am. All standard laboratory parameters plus IGF-1 and interleukin-6 (for NUTRIC score) will be measured along with the morning routine laboratory of the next day. APACHE II, SAPS II and SOFA scores will be assessed within the first 24 h after ICU admission.

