#### Recruitment

The ICU study team will screen every patient with an expected need for enteral nutrition for a minimum of 5 days and a predicted ICU stay of at least 5 days within the first 48 h after ICU admission for study eligibility.

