#### Implementation

The allocation sequence will be generated in collaboration with the clinical trial unit. Recruitment and enrolment of participants will be executed by study team members. The assignment to interventions will automatically be performed by REDCap according to the allocation sequence implemented in the eCRF.

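### As written, the concealment section lets the team that screens and enrols see the allocation sequence, so selection at entry is possible

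*Protocol article*

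**What the plan says.** All references are to the protocol article.

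- **Concealment mechanism.** "The allocation sequence will be uploaded upon study start". The section continues: "As soon as the eCRF is unlocked for real study data entry", "there will be access for the study team to see the sequence".
- **Recruitment.** "The ICU study team will screen every patient with an expected need for enteral nutrition", within 48 h of ICU admission.
- **Implementation.** "Recruitment and enrolment of participants will be executed by study team members". The list is generated together with the clinical trial unit, and "The assignment to interventions will automatically be performed by REDCap according to the allocation sequence implemented in the eCRF".
- **Sequence generation.** Block randomisation, stratified for neurotrauma. Block size is not given.
- **Blinding.** Neither the treating team nor the study team is blinded. Only the statistician analysing the final data is.
- **Inclusion criteria.** Two of the four are forecasts: at least five days of enteral feeding and at least five days in the ICU.
- **Timing.** Table 3 marks randomisation in the screening column (day 0). Participant timeline says "Allocation is defined as the day of start of enteral feeding", which is day 1.

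**The concern.** Concealment means that whoever decides whether and when a patient enters cannot know the next arm. The article says the reverse under the very heading meant to secure it.

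A recruiter who knows the next arm can decline a patient, judge a forecast criterion differently, or use the 48 h window to enter someone else first. None of this needs intent. Three features make it matter here:

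- The forecast criteria leave room for judgement that is not recorded.
- The primary outcome, time to the protein target, depends on tolerance. Counted intake is reduced by half the gastric residual volume, and feeding is halted for high residuals, vomiting, regurgitation or aspiration. Steering patients who look likely to tolerate feeding would shift the outcome directly.
- With 30 patients per group, a few steered patients can move the comparison. Covariate adjustment cannot remove selection on judgements that nobody wrote down.

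**Working it through.** The article gives no figure to reproduce. The check is mainly a reading of the sections against each other.

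**Step 1: who sees the list, and when.** Concealment mechanism names the study team, from the opening of the eCRF for real data. The list is uploaded at study start, so it is complete before the first patient.

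**Step 2: who decides on entry.** Recruitment and Implementation both name the study team. The article does not divide that team into members who may see the list and members who enrol.

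**Step 3: does another section restrict the view?** None does. Implementation says who helps generate the list, not who holds it. Data management gives the study team access to study data without distinguishing roles.

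**Step 4: does any other safeguard compensate?**

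| Safeguard | What it prevents | What it leaves open |
|---|---|---|
| Automatic assignment by REDCap | Changing an arm once assigned | Declining or deferring a patient when the next arm is known |
| Blocks and stratification | Imbalance in numbers | Nothing is hidden if the list is visible, whatever the block size |
| Blinded statistician | Bias in the final analysis | Selection that has already happened |

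Automatic assignment also means that recruiters have no need to see the list.

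**Step 5: size.** With the list visible, the next arm in each stratum is known in 100% of cases. For comparison, take a hidden list in this unblinded single-centre trial. Assume 1:1 allocation, a fixed block size known to the team, and knowledge of past assignments within each stratum. For a block of 2n patients, always guessing the arm that is behind (and tossing a coin when level) gives an expected number of correct guesses of

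E = n + ½ × (4ⁿ / C(2n, n) − 1).

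- Block of 2 (n = 1): 1 + ½ × (4/2 − 1) = 1.5 of 2, or 75%.
- Block of 4 (n = 2): 2 + ½ × (16/6 − 1) = 2.83 of 4, or 71%.
- Block of 6 (n = 3): 3 + ½ × (64/20 − 1) = 4.1 of 6, or 68%.

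Under these assumptions the contrast is 100% against roughly 68 to 75%. If the block size is unknown to the team or varied, guessing is harder and the gap is wider.

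**Step 6: timing of randomisation.** Table 3 puts randomisation on day 0, and Participant timeline puts allocation on day 1. If baseline ultrasound and biopsy cannot be done in time, "the procedures will be postponed to the next day and start of enteral feeding will be the following morning at 6:00 am". Table 3 lists randomisation and the baseline procedures in the same column without an order, so the article does not fix which comes first.

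**The case against.** **A word may have been dropped.** Under this heading, and tied to the unlocking of the eCRF, a sentence denying access would read naturally. The involvement of the clinical trial unit and automatic assignment fit that reading. It is plausible and cannot be excluded. Nothing in the article confirms it, however, and if it is right, the published statement says the opposite of what is meant and still needs correction.

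**Three stronger readings are tempting, and the article does not support them.**

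1. A reader might infer that allocation was in fact unconcealed, or that patients were steered. The article shows what the rule says, not what the REDCap rights were or what anyone did.
2. A reader might set the visible list against a one-in-two chance of guessing the arm when it is hidden. Blocking in an unblinded single-centre trial can make guessing better than that, so one in two is not a safe benchmark.
3. A reader might infer from Table 3 that baseline muscle measures are taken with the arm already known. The table gives no order within the screening column, and dating allocation to the feeding day would put assignment after those measures. This is an ambiguity to reconcile, not a demonstrated flaw. Loss of patients between randomisation and the first feed could also occur under perfect concealment.

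**Conclusion.** The point holds for the text as written. The people who screen and enrol are given sight of the sequence, and no other provision restores concealment. Upcoming assignments are then fully predictable, against about 68 to 75% for a hidden list with known fixed blocks of 2 to 6. That comparator rests on the assumptions stated with it, since the article gives no block size.

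The conclusion covers the rule, not the conduct: selection at entry is possible, and its direction and amount cannot be estimated from the article. Because concealment is basic to a randomised comparison and the correction is simple, the sentence must be fixed whichever reading is true. The timing discrepancy is a separate, lesser matter.

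**What to change.** **Replace the sentence on access** with wording such as: *The allocation table is held by the Clinical Trial Unit or a REDCap administrator who takes no part in enrolment. Nobody who screens, recruits or enrols can view it. REDCap reveals each assignment only after eligibility has been confirmed and the patient irrevocably registered.*

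Then establish which case applies:

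- **Wording slip.** Correct the text and confirm from the REDCap user rights that the team could not view the list. Cost: one sentence and a check of settings.
- **Real access.** Restrict the rights now, regenerate the unused part of the list, and withhold its block sizes from those who enrol. Document who had access and from when; recruitment began in March 2019. Report the access as a limitation, with a comparison of patients enrolled before and after the change. With 60 patients in all, that comparison can reveal gross differences but cannot rule out selection. Cost: an amendment, an access review and a new list, with no added burden on patients.

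**Separately, reconcile Table 3 with Participant timeline** on when randomisation takes place. Where feasible, release the assignment after whichever baseline measures the patient has consented to. It should not depend on a completed biopsy, because the missing-data section lets patients take part without one.

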#### Implementation

The allocation sequence will be generated in collaboration with the clinical trial unit. Recruitment and enrolment of participants will be executed by study team members. The assignment to interventions will automatically be performed by REDCap according to the allocation sequence implemented in the eCRF.

### Assignment of interventions: blinding

A blinding procedure for the treating medical team as well as the study team is not possible. However, the statistician who will analyse the final data will be blinded to the study group.

### Data collection and management

#### Plans for assessment and collection of outcomes

##### Assessment of primary outcome measure

The actual amount of protein intake within the last 24 h after every completed feeding administration cycle will be assessed. The actual amount of protein intake will be calculated according to the volume of the formula administered minus half of the recorded GRV. The decision to subtract half of GRV takes account of the fact that the recorded GRV will always consist of a mixture of nutrition formula and gastric juice. Results will be documented by the nurse responsible for the patient on a study-specific document and transferred to the eCRF, which will be accessible only to members of the study team. Assessment of primary and secondary outcome measures is outlined in Table 3.

##### Ultrasound measurement of quadriceps muscle prior to start of feeding and on day 7 in both study groups

The study team will perform the ultrasound measurements. The teaching for standardised quadriceps ultrasound will be provided and reviewed by the chief consultant of musculoskeletal diagnostics, Department of Radiology, University Hospital Basel.

Tillquist et al. recommend ultrasound imaging for determination of overall muscle mass in ICU patients due to excellent intra- and interrater reliability and the correlation between quadriceps muscle thickness (Q-MT) and overall muscle mass [43]. A linear probe of 5–10 MHz will be used. For comparability with other studies, the thickness of rectus femoris (RF) and vastus intermedius (VI) muscles and the total Q-MT will be measured. In addition, the cross-sectional area of rectus femoris (RF-CSA) will be measured. These parameters were found to be reliable and reproducible in former studies [33, 43–48]. The ultrasound measurements will be performed in the lower third in between the spina iliaca anterior superior and the upper border of the patella [43–45, 47, 49]. As recommended by Thomaes et al. [46], we will use minimal pressure and localise the probe perpendicular to the skin and at long axis of the thigh. Day-to-day consistency will be ensured using skin-compatible ink to mark the measurement sites. The examination will be repeated three times on each leg on both days (during screening (day − 1) and on closeout (day 7)). The mean of the three measurements of each leg will then be calculated and used for analysis.

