**Fig. 1 Fig1:**
[figure not shown]
Study Flow Chart

**Table 3 Tab3:** Study schedule

	Screening	Allocation	Observation time					Closeout
Time	t_−1_	t_0_	t_1_	t_2_	t_3_	t_4_	t_5_	t_6_
Day	0	1	2	3	4	5	6	7
Eligibility criteria	x							
Informed consent	x							
Randomisation	x							
Baseline data	x							
Muscle biopsy and ultrasound	x^1^							x
Start feeding		x^2^						
Vital parameters	x	x	x	x	x	x	x	x
Primary variables		x	x	x	x	x	x	x
Secondary variables^3^	x	x	x	x	x	x	x	x
SAEs		x	x	x	x	x	x	x

^1^Performance of muscle ultrasound and biopsy on inclusion day until 3:00 pm will allow enteral feeding starting the next day at 6:00 am. Whenever the study team is not able to perform both before 3:00 pm, these study procedures will be postponed to the next day and study feeding will start the day after at 6:00 am

^2^6:00 am

^3^Including laboratory parameters, documentation of side effects of enteral feeding and assessment of SOFA score

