#### Data management

Study data will be collected and managed using REDCap electronic data capture tools hosted at University Hospital Basel [50]. REDCap is a secure, web-based application designed to support data capture for research studies. REDCap provides (1) an intuitive interface for validated data entry, (2) audit trails for tracking data manipulation and export procedures, (3) automated export procedures for seamless data downloads to common statistical packages and (4) procedures for importing data from external sources.

All data, including demographic data, visit dates, randomisation number and serious adverse events (SAEs), related to this study will be kept within the trial master file (TMF) and the REDCap eCRF. A unique patient study code will be assigned to every screened patient consisting of the prefix PBN (Pro BoNo) plus consecutive numbering for every included patient (e.g. PBN-1). This code will be used to identify all study-specific data (e.g. ultrasound images, blood parameters). The trial will be terminated after collecting data from 30 patients in each group. The signed informed consent forms will be kept in the investigator site file (ISF). To minimise bias, we will set range checks for data values within the eCRF. Data will be archived dually on an external hard disk and on our in-house server system with a backup every 24 h. The hard disk and all physical study data will be stored in a designated place on our ICU at the University Hospital Basel for a minimum of 10 years after study termination or in case of premature termination of this study.

SAEs will be documented in the REDCap eCRF and on paper documents.

Only the study team will have access to study-related data. In case of a patient’s ex post denial of study participation, the data collected will not be used for publication in the present trial or in future trials. In such cases, the data will be destroyed.

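### Quadriceps ultrasound is measured by a team that knows the arm, and the order of randomisation and the baseline scan is not fixed, so this secondary outcome is open to assessor bias

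*Protocol article*

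**What the plan says.** All references are to the protocol article.

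- **Who measures.** The section on quadriceps ultrasound states: "The study team will perform the ultrasound measurements". The quantities are rectus femoris and vastus intermedius thickness, total quadriceps thickness and rectus femoris cross-sectional area. Each leg is examined three times per visit and the mean is analysed.
- **Who is masked.** The blinding section states: "A blinding procedure for the treating medical team as well as the study team is not possible". It continues: "However, the statistician who will analyse the final data will be blinded to the study group".
- **When randomisation and baseline occur.** Table 3 marks randomisation and the baseline biopsy and ultrasound in the same screening column. Its first footnote adds: "Whenever the study team is not able to perform both before 3:00 pm, these study procedures will be postponed to the next day". The text on the day of inclusion agrees: "Otherwise, the procedures will be postponed to the next day and start of enteral feeding will be the following morning at 6:00 am". No such postponement is stated for randomisation. The participant timeline, by contrast, defines allocation as the day enteral feeding starts.
- **Who can see the sequence.** The concealment section says that once the eCRF is unlocked for real data, "there will be access for the study team to see the sequence".
- **What is stored.** Under data management, ultrasound images are among the data identified by the study code, which is a prefix plus consecutive numbering.

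**The concern.** Thickness and cross-sectional area on ultrasound depend on probe pressure, imaging plane and where the measurement is placed on the image. The people making those choices know which feeding schedule the patient receives. The article also states a direction: it expects more muscle protein synthesis with intermittent feeding. An assessor who shares that expectation can, without intending to, move the day-7 value, and also the baseline value if the arm is already known.

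The outcome is secondary, but it carries weight. The abstract describes the trial as comparing the regimens on preventing muscle wasting, and the strengths section relies on ultrasound together with biopsy for a direct comparison of the two. Patients may decline the biopsy and are not replaced for that, so ultrasound may be the more complete of the two muscle measures. Masking the statistician acts only after the values are recorded.

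**Working it through.** No figure in the article depends on this point, so there is none to reproduce. The check sets the sections side by side.

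**Step 1: day 7.** The ultrasound section gives the measurement to the study team, and the blinding section says that team cannot be masked. The adherence section puts the study group on the bedside protocol. No section provides for a masked operator or reader. The day-7 measurement is therefore unmasked in every patient.

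**Step 2: baseline.**
- Table 3 places randomisation in the screening column, not in the allocation column.
- The scan and biopsy may move to the day after inclusion. For example, a patient included and randomised at 15:01 on day D and scanned by 15:00 on day D+1 is scanned just under 24 h after randomisation.
- The participant timeline links allocation to the first feeding day, which comes after the scan. This does not fit the randomisation row of Table 3.
- The study team can see the sequence, so even if randomisation came later, the arm could be known beforehand.

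The order is thus left open, and a baseline scan with the arm known is permitted.

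**Step 3: do the stated safeguards help?** Write one reading as: true value + arm-related shift b + random error with variance s². The mean of three readings has error variance s²/3, but its shift is (b + b + b)/3 = b. Replication leaves the shift untouched. Training and ink marks reduce variation between operators and sites, but they do not hide the arm.

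For the change from baseline, the bias in the between-arm difference is

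(b at day 7 − b at baseline) in the intermittent arm − (b at day 7 − b at baseline) in the continuous arm.

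A shift that is identical at both visits cancels. One that differs between visits and arms does not.

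**Step 4: size.** The article gives no expected muscle change, no standard deviation and no reader error for ultrasound, so the bias cannot be calculated. The following only shows how sensitive a comparison of this size is. Assume 30 patients per arm (data management section), no true effect, a two-sided z test and a net shift of d standard deviations of the analysed quantity. Then SE = √(2/30) = 0.258 SD, and

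P(reject) = 1 − Φ(z − d/SE) + Φ(−z − d/SE).

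| Assumed d | d/SE | Rejection at α = 0.05 | Rejection at α = 0.01 |
|---|---|---|---|
| 0 | 0 | 5.0% | 1.0% |
| 0.1 | 0.39 | 6.7% | 1.6% |
| 0.2 | 0.77 | 12.1% | 3.6% |
| 0.3 | 1.16 | 21.3% | 7.9% |
| 0.5 | 1.94 | 49.1% | 26.1% |

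Every d above zero is an assumption. The z test is a simplification of the planned repeated measures ANOVA.

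**The case against.** The strongest reply has four parts.

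- **The trial is openly unblinded, and the person scanning at day 7 cannot realistically be kept unaware of the arm.** This stands for acquiring the image. It does not stand for measuring a stored image, which can be separated from the bedside.
- **Table 3 marks days, not the order of steps within a day, and the timeline puts allocation after the scan.** This stands in part. A reader might infer that baseline scans always follow randomisation, and the article does not say so. It leaves the order unfixed, with two sections that disagree and a sequence the team can see.
- **The technique is standardised.** Reviewed teaching, minimal pressure, a perpendicular probe, marked sites and repeats do narrow the operator's discretion. They do not mask.
- **The primary outcome is time to the protein target.** This is correct and limits the weight of the point.

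Three stronger readings are tempting but unsupported. First, a reader might blame the randomisation order for the wait of at least 15 h from the 3:00 pm cut-off to the 6:00 am feed, and for losses during it. That interval lies between the scan cut-off and the first feed and exists whenever randomisation occurs. Loss before the first feed is a question of attrition, not of assessor bias. Second, a reader might express the bias as a share of the expected effect, but neither quantity is in the documents. Third, a reader might extend the point to the biopsy laboratory. The article does not say that the laboratory is told the arm; study-specific data carry a code without it, and another department processes the samples.

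**Conclusion.** The point holds as a risk of bias in a secondary outcome. Day-7 ultrasound is always measured with the arm known, and baseline ultrasound may be. This rests on what the article positively assigns, namely measurement by a team it declares unblindable, and not on detail that a condensed article might leave out. Masking the statistician does not repair it, and the analysis section has the study team itself calculating the results together with the Clinical Trial Unit.

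The documents show that bias is possible, not that it will occur, and its size cannot be derived from them. The table in the working shows sensitivity to assumed shifts and is not an estimate. The change should be made because it is cheap and the muscle comparison is prominent among the trial's claims.

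**What to change.** 1. **Order and concealment.** In Table 3 and the text on the day of inclusion, trigger the REDCap randomisation only after the baseline ultrasound and biopsy are done and before the 06:00 start. Align the definition of allocation in the participant timeline with this. In the concealment section, withdraw the study team's access to the sequence. Both changes are needed: reordering alone does not mask the baseline while the sequence is visible.
2. **Masked reading.** In the blinding and ultrasound sections, state that images are stored unmeasured and relabelled with random numbers that hide patient, arm and visit, with the key held away from the reader. The existing study code is not enough, because its numbering is consecutive. Thickness and cross-sectional area are then measured by an already trained team member who did not scan that patient. A reader outside the team would be stronger, but might need extra staff.
3. **Declared limitation.** State that image acquisition at day 7 (probe pressure and plane) remains unmasked.

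**Cost.** Randomisation in the eCRF is available around the clock, so the first change reorders a step. The second means relabelling files and measuring offline instead of at the bedside. Neither needs new staff or a new patient procedure. The trial status section reports the first patient in March 2019, so the first change helps only patients still to be randomised. The second can also cover earlier images that were kept without measurement marks.
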